### **7.4 NeoRecormon detection assessments**

#### **7.4.1 Urine doping screen**

Please refer to Appendix 7 – Urine doping control procedure for a detailed description of the urine doping control procedure.

### **7.5 RNA expression levels**

In general, genes react to internal or external stimuli by becoming more active, less active or showing no response. Training stimuli induce stress resulting in changes in gene expression patterns. Gene expression (RNA-) profiles made from whole venous blood taken before and after physical exercise differ between non-trained and trained individuals. This suggests that adaptation to training can be assessed using gene expression analysis. Changes in gene expression patterns can then be used to monitor training effects. It is unclear how adaptation to training with or without use of rHuEPO will change gene expression profiles in well-trained individuals. We hypothesize that the changes in these patterns observed in samples taken before and after an exercise test are correlated with the performance and health status of individual athletes. The measurements of maximal and submaximal exercise parameters and clinical laboratory assessments of the participants in this study will be combined with gene expression profile data to investigate if specific changes in the acute response to a submaximal exercise test are correlated with better endurance

performance or other parameters. Comparisons of these profiles in time are expected to reveal the effects of specific types of training and changes in health status.

RNA profiles from whole venous blood samples will be determined using next generation sequencing. Samples for RNA-profiling will be collected around a submaximal intensity test (45 minutes, starting at 80% Power from the baseline maximal exercise test allowing changes to the power at any time by the subject himself if he wishes). Blood samples (2.5 ml) for RNA analysis will be drawn in PAXgene vacuum tubes at 2 time points, before and directly after the test. RNA-profiles made from both time points of each individual will be compared to identify changes in gene expression due to the submaximal intensity test. Profiles from the same time points will also be compared to determine interindividual variation and possible EPO treatment effects.

Expression levels of the different transcripts in the RNA samples will be determined as digital counts using standard bioinformatics pipelines. Cluster analysis and principal component analysis will be performed to determine the relationships between the samples. In this way it will be possible to determine if:

- The expression patterns differ at the time points before and after submaximal exercise test between individuals and between groups.
- rHuEPO treatment does influence gene expression levels.

Multivariate statistics will be applied to analyse and interpret complete RNA-profiles. The leukocyte composition of the original blood samples is correlated with cell-specific transcripts. Therefore, this can be derived from RNA-profiles allowing their correction for this effect.

Comparison with other parameters measured during the study may indicate which changes in gene expression patterns of individuals are correlated with their performance.

For all subjects RNA samples will be collected for potential analyses of gene expression. Instructions for collection, processing, handling and shipment of the samples will be outlined in the laboratory manual. Samples will be archived according to local administration regulations.

Analysis will be performed outside the scope of the main study and reported separately.

## **7.6 Sequence of assessments and time windows**

Assessments will be performed in the following order, where possible: physical examination, weight and height, ECG, vital signs, blood samples, dosing.

The deviations of actual time points from the expected time points will be within ten percent, calculated from the zero point (time of drug administration) or the last relevant activity. Deviations of more than 10% will be explained in a note. Pre-dose assessments are given in indicative expected times.

## 7.7 Total blood volume

| Sample                       | Samples taken |   | Sample Volume*                    |   | Volume          |
|------------------------------|---------------|---|-----------------------------------|---|-----------------|
| Haematology                  | 8             | x | 4 mL                              | = | 32 mL           |
| Chemistry                    | 2             | x | 8.5 mL                            | = | 17 mL           |
| Chemistry short              | 16            | x | 2.5 mL                            | = | 40 mL           |
| Serology                     | 1             | x | 5 mL                              | = | 5 mL            |
| Coagulation                  | 17            | x | 6.2 mL                            | = | 105.4 mL        |
| Coagulation short            | 2             | x | 4.5 mL                            | = | 9 mL            |
| RNA expression               | 2             | x | 2.5 mL                            | = | 5 mL            |
| Biomarker                    | 4             | x | 4 mL                              | = | 16 mL           |
| Hb/Hct (1mL tube)            | 8             | x | 1 mL                              | = | 8 mL            |
| Lactate (Drop)               | 51            | x | 0.8 mL                            | = | 40.8 mL         |
| * inclusive discarded volume |               |   | Total blood volume/subject |   | 278.2 mL |

## **8 SAFETY REPORTING**

### **8.1 Definitions of adverse events**

An Adverse Event (AE) is any untoward medical occurrence in a subject who is participating in a clinical study performed. The adverse event does not necessarily have to follow the administration of a study drug, or to have a causal relationship with the study drug. An adverse event can therefore be any unfavourable and unintended sign (including an abnormal laboratory or vital sign finding), symptom, or disease temporally associated with the study participation, whether or not it is related to the study drug.

#### **8.1.1 Intensity of adverse events**

The intensity of clinical AEs is graded three-point scale as defined below:

- Mild: discomfort noticed but no disruption of normal daily activity;
- Moderate: discomfort sufficient to reduce or affect normal daily activity;
- Severe: inability to work or perform daily activity.

#### **8.1.2 Relationship to study drug**

For each adverse event the relationship to drug as judged by the investigator:

- Probable;
- Possible;
- Unlikely;
- Unrelated.

#### **8.1.3 Chronicity of adverse events**

The chronicity of the event will be classified by the investigator on a three-item scale as defined below:

- Single occasion: single event with limited duration;
- Intermittent: several episodes of an event, each of limited duration;
- Persistent: event which remained indefinitely.

#### **8.1.4 Action**

Eventual actions taken will be recorded.

#### **8.1.5 Serious adverse events**

A Serious Adverse Event (SAE) is defined by the International Conference on Harmonization (ICH) guidelines as any AE fulfilling at least one of the following criteria:

- Is fatal
- Is life-threatening
- Is disabling
- Requires or prolongs in-patient hospitalisation
- Causes congenital anomaly

will be described as a SAE. Important medical events that may not be immediately life threatening or result in death or hospitalisation may be considered a serious adverse event when, based on appropriate medical judgement, they may jeopardise the subject or may require medical or surgical intervention to prevent one of the outcomes listed above.

### **8.1.6 Suspected unexpected serious adverse reactions**

A SUSAR (Suspected Unexpected Serious Adverse Reaction) is a serious adverse event that is unexpected, (nature or severity of which is not consistent with the applicable product information (e.g., investigator's brochure for an unauthorised investigational product or summary of product characteristics for an authorised product)) and suspected (a reasonable possibility of causal relationship with investigational drug).

### **8.1.7 Reporting of serious adverse events**

SAEs and SUSAR's will be reported according to the following procedure.

All SUSARs and SAEs must be reported to the investigator.

In case of multi-centre studies of which a CHDR employee is the responsible investigator, the sub-investigators at sites outside CHDR must notify the investigator by telephone and in writing preferably using a standard form (e.g. CIOMS for SUSARs).

The investigator must report all SAEs and SUSAR's to the EC that approved the study, in writing as soon as practical, but at least within 15 days. Fatal and life-threatening suspected SUSAR's should be reported within 7 calendar days, with another 8 days for completion of the report.

The investigator must report all SUSAR's to the CA, in writing as soon as practical, but at least within 15 days. Fatal and life-threatening suspected SUSAR's should be reported within 7 calendar days, with another 8 days for completion of the report. SAE's do not have to be reported to the CA.

The investigator must furthermore report all SUSAR's to EMA's EudraVigilance database within 15 days. Fatal and life-threatening suspected SUSAR's should be reported within 7 calendar days, with another 8 days for completion of the report.

The investigator can prepare additional reports for other authorities (e.g. FDA).

All SAEs and SUSAR's must be reported on the Toetsing Online website. Fatal and life-threatening SAEs and SUSARs must be reported within 7 calendar days. All other SAEs must be reported within 15 days. By reporting on the Toetsing Online website the EC that approved the study will also be informed.

### **8.1.8 Follow-up of adverse events**

All adverse events will be followed until they have abated, returned to baseline status or until a stable situation has been reached. Depending on the event, follow up may require additional tests or medical procedures as indicated, and/or referral to the general physician or a medical specialist.

## **8.2 Section 10 WMO event**

In accordance to section 10, subsection 1, of the WMO, the investigator will inform the subjects and the EC if anything occurs, on the basis of which it appears that the disadvantages of participation may be significantly greater than was foreseen in the research proposal. The study will be suspended pending further review by the EC, except insofar as suspension would jeopardise the subjects' health. The investigator will ensure that all subjects are kept informed.

## **8.3 Annual safety report or development safety update report**

In addition to the expedited reporting of SUSARs, the investigator will submit, once a year throughout the clinical trial, a safety report to the EC, CA, MEB and CAs of the concerned Member States.

---

 <https://www.toetsingonline.nl/>

This safety report consists of:

- a list of all suspected (unexpected or expected) serious adverse reactions, along with an aggregated summary table of all reported serious adverse reactions, ordered by organ system, per study;
- a report concerning the safety of the subjects, consisting of a complete safety analysis and an evaluation of the balance between the efficacy and the harmfulness of the medicine under investigation.

---

## 9 STATISTICAL METHODOLOGY AND ANALYSES

### 9.1 Statistical analysis plan

All safety and statistical programming is conducted with SAS 9.4 for Windows (SAS Institute Inc., Cary, NC, USA). PK variable programming is conducted with R 2.12.0 for Windows (R Foundation for Statistical Computing/R Development Core Team, Vienna, Austria, 2010).

A Statistical Analysis Plan (SAP) will be written and finalized before the study closure, i.e., database closure and unblinding of the randomization code. The SAP will provide full details of the analyses, the data displays and the algorithms to be used for data derivations.

The SAP will include the definition of major and minor protocol deviations and the link of major protocol deviations to the analysis sets.

### 9.2 Protocol violations/deviations

Protocol deviations will be identified based on conditions related to the categories below:

- Protocol entry criteria
- Forbidden concomitant medications
- Missing evaluations for relevant endpoints
- Other protocol deviations occurring during study conduct.

Major protocol deviations will be identified before the study closure, and listed where appropriate.

### 9.3 Power calculation

Please refer to section 1.4.9.

### 9.4 Missing, unused and spurious data

All missing or incomplete safety and efficacy data, including dates and times, are treated as such. Missing test results or assessments will not be imputed. Missing efficacy data, indicated as 'M' in the data listing, will be estimated within the statistical mixed model using SAS PROC MIXED.

For graphical and summary purposes efficacy and safety values below the limit of quantification will be set to half ( $\frac{1}{2}$ ) of the limit of quantification. For analysis no undetermined values will be replaced. The handling of missing, unused and spurious data will be documented in the study report.

### 9.5 Analysis sets

Data of all subjects participating in the study will be included in the analyses if the data can meaningfully contribute to the objectives of the study.

#### 9.5.1 Safety set

The safety population will be defined as all subjects who were validated (randomised) and received at least 1 dose of study treatment.

#### 9.5.2 Efficacy analysis set

The analysis population for efficacy is defined as all subjects who were validated (randomised), received at least one dose of study treatment, and have at least one post-baseline assessment of the parameter being analysed.

### 9.6 Subject disposition

The following subject data will be summarized by treatment and overall:

- Number and percentage of subjects enrolled in each analysis set for all randomized subjects;
- Number and percentage of subjects who completed the study or prematurely discontinued from the investigational period by reasons for discontinuation, to be tabulated for each analysis set.

Subject disposition will be listed.

## **9.7 Baseline parameters and concomitant medications**

### **9.7.1 Demographics and baseline variables**

Continuous demographic variables (e.g., age, height, weight, BMI) will be summarized by descriptive statistics (n, mean, SD, median, Min, Max). Qualitative demographic characteristics (sex, race/ethnicity) will be summarized by counts and percentages.

The results of the sport activities questionnaire at screening will only be listed.

### **9.7.2 Medical history**

Medical history will only be listed.

### **9.7.3 Concomitant Medications**

Previous and concomitant medications will be coded according to the World Health Organization (WHO) drug code and the anatomical therapeutic chemical (ATC) class code.

All concomitant medications will be displayed in a listing.

### **9.7.4 Treatment compliance/exposure**

Exposure to study treatment is described in terms of duration of treatment and average infusion rate. The average infusion rate (mL/hr) is summarized by mean, SD, median, Q1, Q3, Min, Max.

## **9.8 Safety and tolerability endpoints**

The safety set is used to perform all safety analyses.

Baseline is defined as the last value prior to dosing. Change from baseline will be calculated for all continuous safety parameters.

### **9.8.1 Adverse events**

The AE coding dictionary for this study will be Medical Dictionary for Regulatory Activities (MedDRA). It will be used to summarize AEs by primary system organ class (SOC) and preferred term (PT).

All adverse events will be displayed in listings.

A treatment-emergent adverse event (TEAE) is defined as an adverse event observed after starting administration of the specific treatment, and prior to the start of another treatment, if any OR up to 5 days (96 hours) after study drug administration. If a subject experiences an event both prior to and after starting administration of a treatment, the event will be considered a TEAE (of the treatment) only if it has worsened in severity (i.e., it is reported with a new start date) after starting administration of the specific treatment, and prior to the start of another treatment, if any. All TEAEs collected during the investigational period will be summarized.

The number of and/or the number of subjects with treatment emergent AEs will be summarized by:

1. treatment, MedDRA SOC and PT;
2. treatment, MedDRA SOC, PT and severity;
3. treatment, MedDRA SOC, PT and drug relatedness.

### **9.8.2 Vital signs**

At each time point, absolute values and change from baseline of supine BP and HR will be summarized with n, mean, SD, SEM, median, Min, and Max values. The number of available observations and out-of-range values (absolute and in percentage) will be presented. Values outside the reference range will be flagged in the listing. 'H' and 'L', denoting values above or below the investigator reference range (when present), will flag out-of-range results.

### 9.8.3 ECG

At each time point, absolute values and change from baseline of ECG numeric variables will be summarized with n, mean, SD, SEM, median, Min, and Max values. The number of available observations and out-of-range values (absolute and in percentage) will be presented. Values outside the investigator's normal range will be flagged in the listing. 'H' and 'L', denoting values above or below the investigator reference range (when present), will flag out-of-range results.

### 9.8.4 Clinical laboratory tests

At each time point, absolute values and change from baseline of clinical laboratory variables will be summarized with n, mean, SD, SEM, median, Min, and Max values. The number of available observations and out-of-range values (absolute and in percentage) will be presented. All laboratory data (including re-check values if present) will be listed chronologically. 'H' and 'L', denoting values above or below the investigator reference range (when present), will flag out-of-range results.

## 9.9 Efficacy endpoints

### 9.9.1 Efficacy

The final analysis will be preceded by a blind data review which consists of individual graphs per visit by time of all efficacy measurements by time. The graphs will be used to detect outliers and measurements unsuitable for analysis. The efficacy parameters will be listed by treatment, subject, visit and time. Individual graphs by time will be generated.

All measured PD endpoints will be summarised (n, mean, SD, SEM, median, Min and Max values) by treatment and time, and will also be presented graphically as mean over time, with standard deviation as error bars. All efficacy endpoints will be summarised (mean, SD, SEM, median, Min and Max values) by treatment, and will also be presented graphically as mean in a bargraph, with standard deviation as error bars.

Parameters will initially be analyzed without transformation, but if the data suggest otherwise, log-transformation may be applied. Log-transformed parameters will be back-transformed after analysis where the results may be interpreted as percentage change.

To establish whether significant treatment effects can be detected on the measured efficacy parameters, each parameter that is measured repeatedly will be analyzed with a mixed model analysis of covariance (ANCOVA) with treatment, time and treatment by time as fixed factors and subject, subject by treatment and subject by time as random factors and the (average) baseline measurement as covariate. Parameters that are only measured at baseline and at the end of the treatment phase will be analysed with a one-way ANCOVA with treatment and baseline as covariate.

Single measured efficacy parameters will be analyzed with an unpaired t-test.

The Kenward-Roger approximation will be used to estimate denominator degrees of freedom and model parameters will be estimated using the restricted maximum likelihood method.

The general treatment effect and specific contrasts will be reported with the estimated difference and the 95% confidence interval, the least square mean estimates and the p-value. Graphs of the Least Squares Means (LSM) estimates over time by treatment will be presented with 95% confidence intervals as error bars, as well as change from baseline LSM estimates.

The following contrasts will be calculated within the model:

- NeoRecormon - Placebo

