#### 1.4.3 Study population

Forty-eight well-trained male subjects, 18 to 50 years of age who have a Hb level  $> 8.0$  mmol/L and  $\leq 9.8$  mmol/L, a Ht  $< 48\%$  and a maximal power output  $> 4.0$  W/kg will be included.

Previous studies showed that professional cyclists have Hb concentrations between 8.25 and 10.25 mmol/l and Ht levels between 39.2 and 48.1%. The normal Hb concentration for males is 8.75 to 11.25 mmol/l. The rHuEPO treatment in this study will increase Hb levels of the subjects with 10-15%. Subjects will be excluded during the screening when they have Hb levels  $> 9.8$  mmol/l, because the normal Hb level (11.25 mmol/l) should not be exceeded ( $9.8 \times 1.15 = 11.27$  mmol/l).

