## 6 STUDY ENDPOINTS

### 6.1 Efficacy endpoints

Efficacy will be assessed at the time points indicated in the Visit and Assessment Schedule (Table 1).

Efficacy will be assessed by:

- performance in *exercise tests*
- performance in a *competition*
- measuring markers from the haematological module of the *Athlete Biological Passport*
- measuring *blood flow*

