| Alcohol                    | Alcohol Breath Test                                                                                                                                                                                                                                                                                                                                                                                                                                        | The hand-held Alco-Sensor IV meter (Honac, Apeldoorn, the Netherlands) will be used to measure the breath ethanol concentrations.                                                                     |
| Urine drug screen          | Cocaine, amphetamines, opiates (morphine), benzodiazepines, methamphetamine, MDMA and cannabinoids.                                                                                                                                                                                                                                                                                                                                                        | A urine specimen will be analysed at CHDR by test kit (InstAlert, Innovacon, San Diego, USA).                                                                                                         |

Conjugated bilirubin will be reported only when total bilirubin is outside the reference range.

\*Part of the short chemistry/coagulation panel

The results of the haematology assessment will be used for the safety report and for the athlete's biological passport.

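### The blind data review that judges which measurements are fit for analysis includes each subject's haemoglobin and reticulocyte graphs, from which the arm of most subjects can be inferred

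*Protocol*

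**What the plan says.** Protocol section 9.9.1 places before the final analysis a "blind data review which consists of individual graphs per visit by time of all efficacy measurements by time". Their purpose follows directly: "The graphs will be used to detect outliers and measurements unsuitable for analysis". No efficacy measurement is excepted.

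Section 6.1 lists four efficacy domains. One is "measuring markers from the haematological module of the" Athlete Biological Passport, and the marker list there includes Hb, Ht, red cell count, reticulocyte percentage and count, immature reticulocyte fraction and the OFF-hr score. Section 2.1 puts these markers under the primary objective.

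On the size of the effect, section 1.4.3 states: "The rHuEPO treatment in this study will increase Hb levels of the subjects with 10-15" per cent. Section 1.4.6 describes weekly dose decisions that steer active subjects towards that range.

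Elsewhere the protocol treats the same values as a threat to the blind. Section 5.6.2 sends Hb and Ht reports to a single non-blinded person outside the study, and section 6.2 and synopsis item 17 issue matching dose-change requests for randomly chosen placebo subjects. Section 5.6.1 keeps the randomisation code closed until the database is locked.

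**The concern.** A blind data review protects the analysis only if those deciding which values are usable cannot tell the arms apart. Here the code is closed, but the package contains the time course of the variable that the drug is dosed to change. A reviewer who sees Hb climb by more than a tenth in one subject and stay flat in another will usually guess both arms correctly.

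Most of the other measurements in the package are effort-dependent: VO2max, maximal power, the submaximal test and the race. A low or high value in such data can plausibly be read as a poor effort, a faulty recording or a real result. If the person making that call has a good idea of the arm, the call can lean in either direction. That is the risk the double blind is meant to remove.

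**Working it through.** **1. The plan's own figure.** Section 1.4.3 multiplies the highest eligible screening Hb by the largest expected rise: 9.8 × 1.15 = 11.27 mmol/l. This reproduces. The expected change on active drug is thus 10-15% of the starting value; its midpoint is 12.5%.

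**2. How well Hb alone reveals the arm.** Inputs: rise r = 10, 12.5 or 15% (section 1.4.3); no change on placebo (assumption); the same rise in every active subject (assumption); within-subject CV of Hb of 2-4% (assumption, not in the documents). With one baseline and one late value, the change has SD CV × √2. Cutting midway between the arms gives

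accuracy = Φ( (r/2) / (CV × √2) ).

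| Rise | CV 2% | CV 3% | CV 4% |
|---|---|---|---|
| 10% | 96.2% | 88.1% | 81.2% |
| 12.5% | 98.6% | 93.0% | 86.5% |
| 15% | 99.6% | 96.2% | 90.8% |

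For example, at 12.5% and CV 3%: Φ(6.25/4.243) = Φ(1.473) = 0.930. Among 48 subjects, the 12.5% row means about 0.7, 3.4 or 6.5 wrong guesses; chance would give 24. Averaging three late values raises the row to 99.7%, 96.4% and 91.2%. Reticulocytes, Ht and the OFF-hr score are not used here and can only add information.

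**3. If responses vary.** Let the rise differ between active subjects with SD s of 3-5 percentage points (assumption). Average accuracy becomes ½ [ Φ(6.25/(CV√2)) + Φ(6.25/√(2CV² + s²)) ].

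- CV 2%, s = 3: ½ (0.986 + 0.935) = 96%.
- CV 4%, s = 5: ½ (0.865 + 0.796) = 83%.

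If the rise were only 5%, a single change would classify 81%, 72% or 67% of subjects at CV 2, 3 and 4%.

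**4. What selective exclusion could do.** This is an illustration, not an estimate. Take 22 evaluable subjects per arm and the planned VO2max effect of 1.5/1.95 = 0.77 SD (section 1.4.9.1, both as stated). In each arm drop one value lying 2 SD from that arm's mean, in opposite directions.

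- *Measured once after baseline (time-to-exhaustion test, race):* each arm mean moves 2/21 = 0.095 SD, so the difference moves 2 × 0.095 = 0.19 SD. Baseline adjustment would reduce this.
- *Repeated ramp-test endpoints:* there are four post-baseline tests (section 3.1), analysed in a mixed model with treatment by time. Only one of four visit means moves, so with uncorrelated visits the overall contrast moves 0.19/4 = 0.048 SD, and 0.048/0.77 = 6%.
- *With within-subject correlation ρ (assumption, compound symmetry, baseline covariate ignored):* suppose the subject's three other visits deviate by the expected 2ρ. The model then predicts 6ρ²/(1 + 2ρ) for the missing value, so each visit mean moves (2 − 6ρ²/(1 + 2ρ))/21. At ρ = 0.3 this is (2 − 0.338)/21 = 0.079, and the overall contrast moves 2 × 0.079/4 = 0.040 SD (5%). At ρ = 0.9 it is (2 − 1.736)/21 = 0.0126, and the contrast moves 0.006 SD (1%).

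**The case against.** Four counter-arguments deserve weight.

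*The statistical analysis plan may settle this.* Section 9.1 promises one before unblinding, with full analysis detail, and it is not at hand. Numerical outlier rules belong there, so their absence from the protocol is not a fault. What the protocol itself fixes is the content of the review (all efficacy measurements) and its use. An analysis plan that followed this text would carry the problem forward.

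*The text says detect, not remove.* This is true. Removal is implied by the reference to measurements unsuitable for analysis and by section 9.4, which covers unused and spurious data, but it is not stated outright. The protocol also does not say that one person judges Hb and performance graphs together. It does put them in one package and separates nothing.

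*Inference is not certain.* A reader might conclude that the graphs reveal every subject's treatment. They do not. The classification is probabilistic, rests on an assumed CV, and misses active subjects with small responses.

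*The bias may be small.* A reader might infer a shift of a quarter of the planned effect from 0.19/0.77. That mixes two cases: the 0.77 SD belongs to VO2max, which is measured at four post-baseline visits, while 0.19 SD fits endpoints measured once, for which no planned effect of 0.77 SD exists. Nothing in the text suggests that exclusions would run in opposite directions in the two arms.

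The first and second arguments do not remove the point; the third and fourth limit its size.

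**Conclusion.** The point holds in a limited form. As written, the review in section 9.9.1 is blind to the code while showing reviewers a variable from which the arm of most subjects can be inferred: about 87-99% from one Hb change under a uniform 12.5% rise, no placebo change and a CV of 2-4%, and about 83-96% if the rise also varies with an SD of 3-5 points. Decisions on exercise and race data could be influenced by that inference. The size of any resulting bias is not known. The illustrations put one adverse exclusion per arm at no more than about 0.05 SD on the overall contrast for repeated ramp-test endpoints, and up to about 0.19 SD for endpoints measured once.

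Several wider readings are tempting but unsupported:

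- Section 7.2.6 says "The results of the haematology assessment will be used for the safety report", which might suggest that staff supervising the exercise tests see these results. It names no recipient and no timing, and section 5.6.2 says that study staff stay blinded.
- The phrase "if the data can meaningfully contribute to the objectives of the study" in section 9.5 might look like a licence for subjective exclusion. It only introduces analysis sets that are defined objectively in 9.5.1 and 9.5.2.
- Urine doping results would also reveal the arm, but section 6.1 does not list them as efficacy endpoints, so the review as described does not include them.
- Withholding haematology from the investigator does not follow either: these are safety data (section 6.2), and section 4.6.1 has the investigator act on laboratory abnormalities.

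**What to change.** In section 9.9.1, state that exercise-test and race data are reviewed first and their exclusions are locked and documented before the graphs of the passport haematology markers are opened. Leaving those graphs out of the package used to judge performance data would serve equally well. Add a sensitivity analysis of the exercise and race endpoints with all recorded values.

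The cost is a data review in two steps instead of one, and one extra analysis. No additional data, visits or staff are needed, and safety monitoring is unchanged.
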